# Data Management

*Data collection.* Data forms will initially be field tested for ease of use, ease of analysis, and proper collection of desired information. Questionnaires will be completed by trained household interviewers and health facility recorders. Responses will be written on a hard copy of the questionnaire in ink. After review in the field, hard copies of the questionnaires will be transferred by project vehicles to the site of data entry (see below). Forms should stay in the field no longer than 1 week after completion for review by the field supervisor.

*Data entry and storage.* Data will be collected on scannable forms. Forms will be scanned using a commercial software package (TELEforms Enterprise, Verity) at the CDC/KEMRI field station in Kisian. Scanned data will be reviewed by data specialists and corrected where appropriate using the TELEforms software. A pilot test of paperless data collection using pocket Personal Digital Assistants (PDAs) will be done and compared to the data collected on scannable forms. If this pilot shows that the PDAs are equivalent to scannable forms in data quality, PDAs will be adopted as the primary data collection system. Data from both scannable forms and PDAs will be stored in a database in Microsoft Access and maintained on the network in a restricted drive at Kisian. The database will be routinely backed up. Cleaning programs will be run each week to identify errors in the data collection. When applicable, the forms will be sent back to the field for correction of errors. After data entry, hard copies of forms will be stored in locked long-term storage units in Kisumu (CDC). Access to long-term storage will be restricted to relevant project staff.

*Linkage of household morbidity surveillance data to DSS data.* Data from this study at the Lwak site will be linkable to relevant DSS data (Protocol SSC #647, CDC #3308). Linkage will be based on the DSS ID number of the participating child. This information will be used to compare demographic characteristics of children in zinc and placebo villages, as well as children with diarrhea and without. Permission to link DSS data to data from this study will be requested in the informed consent form (see below).

*Linkage of laboratory results and morbidity surveillance data.* On-going surveillance for diarrheal disease among children will continue in Lwak clinic (protocol SSC#381 , CDC#2616). As part of this protocol, all persons presenting with diarrhea to one of 6 clinics in Asembo and Gem, including Lwak, who can produce stool while in the clinic, will have a stool culture sent to the lab at Kisian for microbiologic identification and antimicrobial susceptibility testing. These results will be able to be linked to the zinc study by ID number of the individual, which will be present on all forms. Permission to link microbiologic stool data to data from this study will be requested in the informed consent form (see below).

*Data access.* Data in Kisumu will be accessible to a limited number of relevant CDC/KEMRI and ICDDRB staff.

*Confidentiality of data.* Data will be kept as confidential as permitted by law. Hard copies of questionnaires will be stored at all times in a room that will be locked when not occupied. Access to these files will be limited to relevant persons. Electronic copies of the data will be kept in the above-mentioned databases, which will only be accessible to relevant CDC/KEMRI and ICDDRB staff and will be password protected.

Data Analysis

All statistical analyses will be performed using SAS system for Windows (SAS Institute, Cary, NC).

*Calculation and comparison of prevalence rates*

Prevalence rates of diarrheal disease will be calculated as number of diarrheal days per person-time. Using person-time as the denominator can incorporate information from children who are in the study for only part of the time, contributing less than 1 full year of data, due to out-migration, death or birth. Curves of monthly prevalence rates of diarrhea will be calculated and plotted for home zinc and nonhome zinc villages. 95% confidence intervals will be calculated around these point estimates of prevalence rates. Because of the study design in which zinc will be given only for the treatment of diarrhea, the preventive effects of zinc will likely become more apparent with time as more children receive zinc. Therefore, initially the prevalence will be the same. With time, the prevalence might diverge between the study groups. Prevalence rates over time between the home zinc and nonhome zinc groups will be compared using Poisson regression applying the generalizing estimating equation (GEE) technique to account for the repeated measures design and control for correlation of diarrheal days among individuals. The Wald test will be used to evaluate the parameter that estimates the effect of treatment group. Statistical significance will be considered at the 0.05 level. Potential confounders of the outcome, such as village of residence and age of the child , will be controlled for in the final model.

Prevalence rates for clinically suspected acute respiratory illness based on the caretakers reports every 2 weeks will be calculated in the same way as for diarrhea.

In addition, we will analyze the cumulative dose effect (total number of zinc days) on the prevalence of diarrhea among individuals in the zinc villages using poisson regression with total number of zinc days as the independent variable.

## Calculation and comparison of incidence rates

Incidence density rates of diarrheal disease will be calculated as number of new episodes of diarrhea per person-time. Using person-time as the denominator can incorporate information from children who are in the study for only part of the time, contributing less than 1 full year of data, due to out-migration, death or birth. 95% confidence intervals will be calculated around point estimates of incidence rates. Incidence rates for acute respiratory illness and malaria will be calculated in the same way as for diarrhea. The mean number of episodes of diarrhea will be compared between the home zinc and nonhome zinc groups using an ANOVA test accounting for repeat episodes of diarrhea within the same child, accounting for potential confounding variables, such as age and season. Potential confounders of the outcome, such as village of residence and age of the child and malaria coinfection, will be controlled for in the final model.

*Calculation and comparison of time to repeat episode of diarrhea.*

The time before a repeat episode of diarrhea in children who have their first episode of diarrhea will be compared between the home zinc and no home zinc groups. The time to a new episode of diarrhea will be measured as the number of days after the last day of the child’s first episode of diarrhea to the first day of the next episode of diarrhea in that child. This analysis will use as a Cox proportional hazards model, in which the child will be censored after the first day of their first repeat episode of diarrhea.

A secondary analysis will compare the number of repeat diarrheal episodes that occur after the first episode of diarrhea. Mean or median number of repeat episodes will be compared by t-test or Wilcoxon rank sum test depending on the distribution of episodes.

*Comparison of the effect of zinc on the treatment of diarrhea.* The mean duration of diarrheal episodes between children in the home zinc and nonhome zinc groups will be compared using ANOVA controlling for potential confounders such as age and season. Repeat episodes of diarrhea in the same children will be accounted for in the analysis. We will also analyze differences in the severity of diarrhea between groups (severe defined as visiting the clinic) and antibiotic use between groups. This will be done using logistic regression with clinic visit and use of antibiotic as the outcome variable.

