# Study design

*Study site and population* -- This study will take place the area of Asembo within 4.25 kilometers of Lwak Hospital where CDC’s IEIP program has ongoing population-based surveillance for infectious disease syndromes.

Since September 2001, KEMRI and CDC have collaborated to operate a demographic surveillance system (DSS) in Bondo and Siaya Districts in Western Kenya. Two rural study sites near Lake Victoria, Asembo and Gem, are covered by the DSS, totaling a population of approximately 130,000 people living in approximately 34,000 households. The area is large (almost 400 km2), culturally homogeneous (95% Luo tribe); subsistence farming and fishing constitute the principal economy. The area has perennial, high-level malaria transmission and a high rate of HIV infection (2003, >10% men, >20% women aged 13-34 years). Other infectious diseases are also common in the area. Consequently, the area has mortality figures that reflect this burden of infectious diseases --- infant mortality rate (120 per 1,000 live births) and a life expectancy at birth of 38 years. The area is one of the most impoverished in Kenya; 60-70% of people live below the poverty line in Siaya and >70% in Bondo (Kenyan Central Bureau of Statistics, 1997). The area has high rates of migration -- in 2002, the rate of out-migration was 115 per 1,000 person-years and in-migration was 124 per 1,000 person-years.

The Lwak surveillance area includes 33 villages, with an approximate enrolled population of 23,000 people. Enrollment of villages began in October 2005 and was completed in June 2006. Homes are visited every two weeks by field workers who enquire about symptoms of key infectious diseases, like diarrhea, respiratory infections and malaria. For key symptoms, like diarrhea, cough and fever, the actual number of days of symptoms are recorded. Some basic measurements, such as temperature and respiratory rate, are taken. Health seeking in the last two weeks is also asked about. This is being done for children and adults.

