## Sample size.

*Diarrhea Prevalence*.

The below calculations are for our primary study outcome of diarrhea prevalence.

Table 2a. Sample size estimates for various prevalences and reductions. Sample size table assumes a 5% reduction in diarrhea prevalence in the control group with a difference of 15% - 10% between groups.

| Difference in groups | Initial Prevalence in each group | N for each group initially/Total N | N for each group at end of trial/ Total N  (with 15% attrition) |
| --- | --- | --- | --- |
| 15% | 3.6 | 1059/2118 | 900/1800 |
| 14% |  | 1184/2368 | 1006/2012 |
| 13% |  | 1318/2636 | 1120/2240 |
| 12% |  | 1435/2870 | 1219/2438 |
| 11% |  | 1651/3302 | 1403/2806 |
| 10% |  | 3036/6072 | 2580/5160 |

Table 2b. Sample size estimates for various prevalences and reductions Sample size table assumes a 10% reduction in diarrhea prevalence in the control group with a difference of 15% - 10% between groups.

| Difference in groups | Initial Prevalence in each group | N for each group initially/Total N | N for each group at end of trial/ Total N  (with 15% attrition) |
| --- | --- | --- | --- |
| 15% | 3.6 | 1550/3100 | 1317/2634 |
| 14% |  | 1745/3490 | 1483/2966 |
| 13% |  | 1978/3956 | 1681/3362 |
| 12% |  | 2259/4518 | 1920/3840 |
| 11% |  | 2798/5596 | 2378/4756 |
| 10% |  | 4118/8236 | 3500/7000 |

We will assume 3.6 episodes per year of diarrhea in children in the study area, with an average duration of 3 days +/- 1 day. This gives a yearly prevalence of diarrhea of 10.8 days of diarrhea per child per year with a range of 7.2 to 14.4 days. We will also assume that because zinc use will increase gradually in the zinc villages as more children get diarrhea, it will take 6 months to achieve the indicated difference in diarrhea prevalence between the two groups (column 1). In the top table, it is assumed that there will be 5% reduction in diarrhea prevalence in the control group (nonhome zinc group) between the start of the study and end of the study 12 months later, due to the implementation of zinc in the clinic. The bottom table assumes that this reduction in the control group over the 12 months will be 10%.

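### Diarrhea incidence is defined per person-time, but the named between-arm test is an ANOVA on mean episode counts that does not carry person-time

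*Protocol*

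**What the plan says.** The incidence section of the protocol's Data Analysis opens with the measure: "Incidence density rates of diarrheal disease will be calculated as number of new episodes of diarrhea per person-time". Its reason for a person-time denominator is that some children will be in the study for only part of the time, "contributing less than 1 full year of data, due to out-migration, death or birth".

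The section then names one comparison between arms for incidence: "The mean number of episodes of diarrhea will be compared between the home zinc and nonhome zinc groups using an ANOVA test". That sentence continues: "accounting for repeat episodes of diarrhea within the same child, accounting for potential confounding variables, such as age and season". The next sentence adds village of residence, age and malaria coinfection as covariates in a final model. No offset, weight or rate outcome is mentioned. Nor is it said whether an observation is one total per child or a count per child and period.

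The preceding section treats prevalence, also defined per person-time, differently. Those rates "will be compared using Poisson regression applying the generalizing estimating equation (GEE) technique".

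**The concern.** The measure and the test do not match. A mean number of episodes depends on both the episode rate and the length of observation. A child seen for one month and a child seen for twelve contribute equally to the mean, although their expected counts differ twelvefold. The paragraph recognizes this when it chooses person-time, and then names a test without it.

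Two consequences could follow. Variation in follow-up adds noise to the comparison. Any difference in follow-up between the arms also shifts the mean counts, whether or not zinc at home changes the rate. Because the unit of analysis is open, a reader also cannot tell how the promised handling of repeat episodes and season would be carried out.

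This is not a detail left for an analysis plan. The protocol fixes both the outcome (a mean number) and the test (ANOVA).

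**Working it through.** **Inputs from the protocol**
- Episode rate and duration (Sample size): "We will assume 3.6 episodes per year of diarrhea in children in the study area, with an average duration of 3 days +/- 1 day".
- Migration (Study design), for 2002, all ages, whole surveillance area: "the rate of out-migration was 115 per 1,000 person-years and in-migration was 124 per 1,000 person-years".
- Follow-up of 1 year (Abstract). Children born into the area may join at 2 months of age (Inclusion criteria).
- Significance level 0.05, stated for the prevalence analysis. Two-sided is assumed here.
- About 3,000 children (Sample size) or about 1,300 (Abstract), so about 1,500 or 650 per arm.

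**The plan's own figure.** 3.6 × 3 = 10.8 diarrhea days per child-year, with range 3.6 × 2 = 7.2 to 3.6 × 4 = 14.4. This reproduces. The protocol gives no sample size or power for incidence.

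**Share with part-year follow-up, migration alone.** Per baseline child, 1 − exp(−0.115) = 0.109 leave within the year and 0.124 arrive. If arrivals are enrolled, the share is (0.109 + 0.124) / 1.124 = 0.21. Simply adding the two rates gives 0.115 + 0.124 = 0.24.

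If arrivals are not enrolled but births are, and ages are uniform over 2 to 60 months, new entrants are 12/58 = 0.207. The share is then (0.207 + 0.109) / 1.207 = 0.26.

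**Precision when follow-up is balanced.** Let T be a child's follow-up in years, λ = 3.6, and v the variance of a child-level rate multiplier with mean 1 (the frailty variance).
- Variance of a count: λE[T] + λ²vE[T²] + λ²Var(T).
- Variance relevant to the rate (of Y − λT): λE[T] + λ²vE[T²].
- Ratio of the two: 1 + λVar(T) / (E[T] + λvE[T²]).

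Suppose a share p is followed for a time uniform on 0 to 1 year and the rest for the full year. Then E[T] = 1 − p/2, E[T²] = 1 − 2p/3 and Var(T) = p/3 − p²/4.

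For p = 0.30: E[T] = 0.85, E[T²] = 0.80, Var(T) = 0.0775 and λVar(T) = 0.279. With v = 0.3 the ratio is 1 + 0.279 / (0.85 + 0.864) = 1.16. With v = 1 it is 1 + 0.279 / (0.85 + 2.88) = 1.07.

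| p | v = 0 | v = 0.3 | v = 1 |
| --- | --- | --- | --- |
| 0.15 | 1.17 | 1.08 | 1.04 |
| 0.21 | 1.24 | 1.12 | 1.05 |
| 0.30 | 1.33 | 1.16 | 1.07 |
| 0.40 | 1.42 | 1.21 | 1.10 |

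**Shift when follow-up differs.** Take equal true rates and mean follow-up of 0.85 year in one arm and 5% less in the other. The mean counts are 3.6 × 0.85 = 3.06 and 3.06 × 0.95 = 2.907, an apparent 5% reduction. A 10% difference gives 2.754, an apparent 10% reduction.

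**Rejection rates.** 1,000 trials were simulated per setting, comparing raw counts with rates (robust standard error). Assumptions not in the protocol: uniform ages, exit at 60 months, v = 1, no village clustering, no age covariate. In this cohort about 47% of children have part-year follow-up and the mean is 0.76 year.

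| Setting | Counts, 1,500 per arm | Rates, 1,500 per arm | Counts, 650 per arm | Rates, 650 per arm |
| --- | --- | --- | --- | --- |
| Equal rates, equal follow-up | 0.040 | 0.052 | 0.057 | 0.054 |
| Equal rates, 5% less follow-up in one arm | 0.244 | 0.047 | 0.115 | 0.038 |
| Equal rates, 10% less | 0.708 | 0.052 | 0.410 | 0.057 |
| Rate ratio 0.88, equal follow-up | 0.864 | 0.901 | 0.499 | 0.554 |

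**The case against.** **Balance.** Villages are randomized within one area that the protocol describes as culturally homogeneous, and nothing in it predicts different migration, births or deaths by arm. This stands. A reader might infer that the ANOVA is biased as planned, but the documents do not support that. With equal follow-up it held its size in the simulation, so the skewness of counts is no separate problem at these numbers. The 5% and 10% differences are illustrations. With only 33 villages, a chance imbalance is possible but not shown.

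**Age adjustment.** Late entry by birth is tied to age, which the plan adjusts for. This would absorb part of any shift. The simulation did not include it, so its rejection rates are for an unadjusted test. Age adjustment does not address follow-up lost through migration.

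**Season.** A reader might infer that the ANOVA cannot adjust for season. That holds only if each child supplies one annual total, which the protocol does not say. The clause about repeat episodes can be read as a repeated-measures analysis by period, and symptoms are recorded by day (Appendix C). What stands is that the unit is unstated.

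**Size of the precision loss.** The v = 0 column, up to 42%, assumes that all children share one rate. The Sample size section says that some children are more prone to repeated episodes, so that column should not be relied on.

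**Benchmark.** The 12% and 15% differences in the Sample size section are for prevalence. The protocol sets no target for incidence, and 0.88 is used above only as an example.

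**Importance.** Overall incidence is not a listed objective. Recurrent diarrhea is, and it has a Cox model that can handle unequal follow-up. Person-time rates with confidence intervals are also planned. All this limits the weight of the point but does not make the named test compare those rates.

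**Conclusion.** The point holds in limited form. The incidence section defines a rate per person-time and then tests a mean count without it, so the named test does not estimate the rate ratio. The unit of analysis is open, which leaves the handling of repeat episodes and season unclear.

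If follow-up is balanced between arms, the cost is precision only. For part-year shares of 15% to 40%, it is about 8% to 21% more variance at frailty variance 0.3 and about 4% to 10% at 1. In the simulation, power fell by about 4 to 5 points at a rate ratio of 0.88. If follow-up is unbalanced, the mean counts shift by about the same percentage as the person-time.

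The frailty values, the part-year shares, their uniform spread and any imbalance are assumptions. The 21% to 24% share rests on 2002 all-age migration rates and on arrivals being enrolled. The analysis is secondary, and the primary prevalence analysis is not affected.

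**What to change.** Replace the ANOVA sentence with a Poisson or negative binomial regression, fitted by GEE as already planned for prevalence. State the unit as the child-period, for example the child-month. Use log person-time as offset, include calendar month and age as covariates, and take village, the randomized unit, as the clustering unit. Report the incidence rate ratio for home versus no home zinc with its 95% confidence interval.

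This makes the test match the stated measure, gives season and repeat episodes a defined place, and removes the dependence on equal follow-up. The cost is a change of wording: daily symptom data are already collected in Appendix C, and the software and model family are already planned.

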Clinical Effectiveness and Preventive Impact of Home Zinc Treatment for Acute Diarrhea in Children: A Cluster-randomized Field Trial in Rural Western Kenya

KEMRI SSC # 985; CDC IRB # 4678

Amended August 27, 2007

Investigators.

[name], MSPH, Epidemiology Section Chief, CDC International Emerging Infections Program, Kenya.

[name], SUZY Project Principal Investigator, Director, Health Systems & Infectious Diseases Division, International Center for Diarrheal Disease Research (ICDDR,B), Bangladesh

[name], Director, CDC International Emerging Diseases Program Kenya.

[name], BSc. Nutritionist, CDC/KEMRI.

[name]. Malaria Branch Chief, CDC/KEMRI Field Station, CDC

[name]. CDC/KEMRI Field Station Director, Kisumu Kenya

[name]. Director, Division of Child Health, Kenya Ministry of Health.

[name]. Director, Centre for Vector Biology and Control Research, Kenya Medical Research Institute

[name], Director, CDC/KEMRI Field station, Kisumu, Kenya

Abstract.

Background. Zinc deficiency is common in Africa. It has been shown in Asia that zinc as treatment for diarrhea can shorten the course of episodes of diarrhea, as well as prevent future episodes. The use of zinc at home to treat diarrhea in an African setting, where malaria, HIV and malnutrition are common, has not been well-studied.

Objective. To evaluate if zinc treatment for diarrhea given at home in Kenyan children will decrease the community prevalence of diarrhea more than zinc given only in the clinic

Work planned. We propose to do a community-randomized intervention study of 10 days of dispersible zinc tablets given in the home, in addition to ORS, to treat diarrhea in children under-5 years of age living in a rural part of Bondo District. The comparison group will be children who receive zinc and ORS in the clinic only. The primary outcome will be a comparison of the prevalence of diarrhea in home zinc versus nonhome zinc villages. Secondary outcomes will be the incidence of repeat episodes of diarrhea, the duration of diarrheal illness, the prevalence of acute respiratory infection, and the effect of malaria infection on treatment with zinc. Thirty-three villages (approximately 1300 children) will be enrolled and children will be followed for 1 year.

Significance of results. If this study shows zinc given at home to be effective, this might be considered by the Kenyan MOH as an essential component of the treatment of diarrhea in children at the community level.

Background.

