## Secondary

1. To assess if access to zinc treatment for diarrhea in the home in addition to zinc treatment of diarrhea in the clinic decreases the likelihood of recurrent diarrhea episodes
2. To assess if access to zinc treatment for diarrhea in the home in addition to zinc treatment of diarrhea in the clinic leads to a reduction in the prevalence of acute respiratory infections
3. To assess if access to zinc treatment for diarrhea in the home in addition to zinc treatment of diarrhea in the clinic results in reduction in antimicrobial use
4. To assess whether treatment of diarrhea with zinc in the clinic leads to a decrease in diarrhea prevalence from baseline rates of diarrhea before introduction of zinc
5. To assess difference in zinc utilization practices in parent initiated home treatment vs clinic treatment communities
   1. frequency of use and adherence to treatment instructions
   2. who receives zinc
   3. used for what indications
6. To compare cost estimates and estimate cost benefits
7. To assess acceptability and satisfaction with a home treatment program among providers and caretakers

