In this repeated measures, longitudinal study design, correlation between events must be accounted for. That is, some children will be more likely to have repeated diarrheal episodes and so will contribute disproportionately to the community prevalence. To do this, sample size calculations accounted for correlation by using the generalized estimating equation (GEE) method described by Rochon (Rochon J, 1998).

Approximately 14% of enrolled participants in the morbidity surveillance study are under 5 years of age. Therefore, we would expect in a population of 25,000 enrolled participants in the 33 villages in Lwak approximately 3,000 children under 5 years. Therefore, we will have the power to detect a difference of 12% between home zinc and nonhome zinc groups, assuming a 5% decrease in diarrhea prevalence in the nonhome zinc group during the study period, or a 15% difference between the home zinc and nonhome zinc groups, assuming a 10% decrease in diarrhea prevalence in the nonhome zinc group over the study period.

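### The recurrence Cox model stops at the first repeat episode and uses about 22-33% of repeats; the only analysis of all repeats after the first episode is a count test without person-time or village clustering

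*Protocol*

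**What the plan says.** Secondary objective 1 (Protocol, Objectives, Secondary) asks whether home access to zinc "decreases the likelihood of recurrent diarrhea episodes".

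Under Data Analysis, the paragraph on time to a repeat episode measures the interval from the last day of a child's first episode to the first day of the next. It compares arms with a Cox model in which "the child will be censored after the first day of their first repeat episode of diarrhea". I read this as counting the first repeat as the event and ending follow-up there.

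The next paragraph adds: "A secondary analysis will compare the number of repeat diarrheal episodes that occur after the first episode of diarrhea". The test is a t-test or Wilcoxon rank sum test, chosen by the distribution. Neither paragraph mentions village, and the count comparison does not mention time at risk.

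The same section also plans an incidence analysis: "Incidence density rates of diarrheal disease will be calculated as number of new episodes of diarrhea per person-time". That covers first and later episodes together.

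The Sample size section supplies the rate ("We will assume 3.6 episodes per year of diarrhea in children in the study area") and says that children differ: "some children will be more likely to have repeated diarrheal episodes and so will contribute disproportionately to the community prevalence". The Abstract gives the follow-up: "Thirty-three villages (approximately 1300 children) will be enrolled and children will be followed for 1 year". No effect size, event count or power is stated for recurrence.

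**The concern.** With several episodes expected per child in a year, a model that ends at the first repeat leaves most of the relevant events out. A real reduction in recurrence could then be reported as not significant.

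The natural safeguard is the planned count comparison, since it uses every repeat. But it treats children as independent although villages are randomized, and it ignores that children have different time at risk after their first episode. Objective 1 is therefore served by one analysis that is inefficient and one whose p-value cannot be relied on if villages differ.

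**Working it through.** **Inputs.** From the protocol: 3.6 episodes per child-year; episodes "with an average duration of 3 days +/- 1 day"; 1 year of follow-up; 33 villages, 16-17 per arm; about 1,300 children (Abstract) or about 3,000 (Sample size), so both are run. Assumed, because the protocol gives no value: gamma variance between children θ = 0 to 1; village log-SD 0 to 0.2 (also village CV up to 0.25); rate ratio 0.88, borrowed from the 12% difference for the primary outcome.

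**1. The protocol's own figure.** 3.6 × 3 = 10.8 diarrhea days per child-year, with range 3.6 × 2 = 7.2 to 3.6 × 4 = 14.4. All three match the Sample size section.

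**2. Share of repeats that the Cox model uses.** With N episodes in the year, the share is P(N ≥ 2) / E[(N − 1)⁺], where E[(N − 1)⁺] = 3.6 − 1 + P(N = 0).
- θ = 0: P(N = 0) = e^−3.6 = 0.027; P(N ≥ 2) = 1 − 0.027 × 4.6 = 0.874; share = 0.874 / 2.627 = 33%.
- θ = 0.25: 0.778 / 2.677 = 29%.
- θ = 0.5: P(N = 0) = 2.8⁻² = 0.128; share = 0.708 / 2.728 = 26%.
- θ = 1: 0.612 / 2.817 = 22%.

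With half a year of follow-up (mean 1.8), the share is 0.537 / 0.965 = 56% at θ = 0 and 0.461 / 1.077 = 43% at θ = 0.5. The problem is smaller for children observed for less time.

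**3. Power.** Simulations used 33 villages (17 against 16) with 91 or 39 children each, θ = 0.5, ratio 0.88 acting after the first episode, and village-robust standard errors for both methods. Two separate runs are shown, each as first-repeat Cox against all repeats.

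| Children | Village log-SD | Run A | Run B | Loss (points) |
|---|---|---|---|---|
| 3,000 | 0 | 65% vs 97% | 66% vs 96% | 30-32 |
| 3,000 | 0.1 | 54% vs 78% | 49% vs 72% | 23-24 |
| 3,000 | 0.2 | 33% vs 40% | 32% vs 38% | 6-7 |
| 1,300 | 0 | 32% vs 68% | 34% vs 64% | 30-36 |
| 1,300 | 0.1 | 27% vs 51% | 28% vs 49% | 21-24 |
| 1,300 | 0.2 | 23% vs 33% | 20% vs 32% | 10-12 |

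With 3,000 children and village CV 0.25, the figures are 30% against 32%. With 3,000 children, a 30% effect and CV 0.15, power is at least 99.7% either way.

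**4. False positives of the count test.** At θ = 0.5 the repeat count has mean 2.728 and variance (23.04 − 7.2 + 1 − 0.128) − 2.728² = 9.27. Its mean changes by 3.6 − 3.6/2.8³ = 3.44 per unit of log rate.
- Village log-SD 0.1: intraclass correlation ≈ 0.344² / (9.27 + 0.344²) = 0.0126.
- Village log-SD 0.2: 0.687² / (9.27 + 0.687²) = 0.0485.

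The design effect is 1 + (n − 1) × correlation, and the true size of a nominal 5% test is 2[1 − Φ(1.96/√design effect)].
- Log-SD 0.1: design effect 1.48 (n = 39) and 2.13 (n = 91); size 11% and 18%.
- Log-SD 0.2: 2.84 and 5.36; size 24% and 40%.

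Simulation of the t-test under no effect gave 10-39% over the same range, and the Wilcoxon test gave 9-32%.

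**The case against.** The strongest reply is that the plan as a whole leaves nothing out. The count comparison uses every repeat, and the incidence analysis uses every episode. With no village variation, the planned t-test has simulated power of 92% with 3,000 children and 58% with 1,300 at ratio 0.88, which recovers most of what the Cox model loses. This stands, and it rules out any claim that later repeats are discarded from the trial. But the rescue works only if villages do not differ. Once they do, the t-test no longer holds its 5% level. The incidence analysis pools first episodes with repeats, so it does not isolate recurrence.

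A reader might also infer that the Cox model is biased toward no effect. The documents do not support that. With no variation between children, a true ratio of 0.85 comes back as 0.851. With assumed variance 0.5, 0.88 becomes about 0.90, but this is the difference between a marginal and a within-child effect. It needs a degree of heterogeneity that the protocol asserts without quantifying.

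A third inference is that the dropped episodes are those where the protocol expects the greatest benefit. The Data Analysis text on prevalence ties the growing effect to more children receiving zinc over time, not to repeated courses in one child.

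Finally, objective 1 speaks of likelihood, which time to first repeat does address. That is why it is worth keeping.

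**Conclusion.** The point holds as one of efficiency and test validity. At the protocol's own rate over a full year, the Cox model uses 22-33% of repeat episodes, and the companion test as worded is not a sound substitute in a village-randomized trial.

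The power loss depends on inputs that the protocol does not give. At ratio 0.88 and between-child variance 0.5 it is about 30-36 points with no village variation, 21-24 at log-SD 0.1 and 6-12 at 0.2. With larger village variation it becomes small, because differences between villages then limit both methods. With 3,000 children and a 30% effect it is negligible. It should therefore not be described as a large loss in every case. Nothing here shows the protocol contradicting itself, and the primary outcome is not affected.

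**What to change.** Make the main recurrence analysis a recurrent-event model, either an Andersen-Gill Cox model or a rate model, over all repeat episodes. Each child enters after the last day of the first episode and stays at risk until leaving the study, excluding days within an episode and the 72-hour window that defines a new one. Use a robust variance clustered on village. Keep time to first repeat as a supplement, also with village-clustered variance, and drop the unadjusted count test.

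The cost is a change of analysis wording and a little more programming; the household morbidity form (Appendix C) already records diarrhea by day. The downside is that the estimate becomes an average over all repeats, so children with many episodes count for more. The robust variance allows for their correlation but does not change that weighting, which the report should state.
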